# Assessment of Autologous Blood marker localIzation and intraoperative coLonoscopy localIzation in laparoscopic colorecTal cancer surgery (ABILITY): a randomized controlled trial

**DOI:** 10.1186/s12885-023-10669-w

**Published:** 2023-03-03

**Keywords:** Colorectal cancer, Laparoscopic surgery, Tumor localization, Endoscopic tattooing, Autologous blood, Intraoperative colonoscopy

## Abstract

**Background:**

Laparoscopic colorectal surgery has been proved to have similar oncological outcomes with open surgery. Due to the lack of tactile perception, surgeons may have misjudgments in laparoscopic colorectal surgery. Therefore, the accurate localization of a tumor before surgery is important, especially in the early stages of cancer. Autologous blood was thought a feasible and safe tattooing agent for preoperative endoscopic localization but its benefits remain controversial. We therefore proposed this randomized trial to the accuracy and safety of autogenous blood localization in small, serosa-negative lesion which will be resected by laparoscopic colectomy.

**Methods:**

The current study is a single-center, open-label, non-inferiority, randomized controlled trial. Eligible participants would be aged 18–80 years and diagnosed with large lateral spreading tumors that could not be treated endoscopically, malignant polyps treated endoscopically that required additional colorectal resection, and serosa-negative malignant colorectal tumors (≤ cT3). A total of 220 patients would be randomly assigned (1:1) to autologous blood group or intraoperative colonoscopy group. The primary outcome is the localization accuracy. The secondary endpoint is adverse events related to endoscopic tattooing.

**Discussion:**

This trial will investigate whether autologous blood marker achieves similar localization accuracy and safety in laparoscopic colorectal surgery compared to intraoperative colonoscopy. If our research hypothesis is statistically proved, the rational introduction of autologous blood tattooing in preoperative colonoscopy can help improve identification of the location of tumors for laparoscopic colorectal cancer surgery, performing an optimal resection, and minimizing unnecessary resections of normal tissues, thereby improving the patient’s quality of life. Our research data will also provide high quality clinical evidence and data support for the conduction of multicenter phase III clinical trials.

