### Hypothesis

Preoperative endoscopic localization with autologous blood is no inferiority to intraoperative colonoscopy localization in small, serosa-negative lesion which will be performed by laparoscopic colectomy.

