#### Secondary outcomes

The secondary endpoint, which is adverse events related to endoscopic tattooing, such as perforation, abscess formation, peritonitis, post-tattoo fever, post-tattoo abdominal pain, and intraperitoneal spillage of tattooing agent, will be evaluated in autologous blood group. Surgery related complications include peritoneal effusion or abscess formation, hemorrhage (inside abdominal cavity, inside digestive tract), ileus, anastomotic leakage, intestinal fistula, lymphatic leakage, gastroparesis, pancreatitis, lung infection, pleural effusion, urinary tract infection, renal failure, liver failure, cardio-cerebrovascular events (both lower extremities thrombosis, pulmonary embolism, myocardial infarction, arrhythmia, cerebral infarction, etc.), and others. Surgical complications will be evaluated in both groups. Complications will be reported and graded according to the Clavien-Dindo classification of surgical complications.

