### Sample size and statistical analysis

The primary objective of this study is to identify non-inferiority of autologous blood tattooing versus intraoperative colonoscopy group. Based on our current experience and previous studies which reported the rates of successful visualization, success rates of 99 and 95% were assumed for the intraoperative colonoscopy group and the autologous blood group, respectively. With settings of 80% power, 5% significance level, and non-inferiority margin of 10%, sample sizes of 110 patients in each group will be required.

Continuous variable will be presented as mean and SD if normally distributed, or as median and range otherwise. The differences between the groups were assessed using the t-test, the Mann-Whitney test, Fisher’s exact test, or the χ2 test, as appropriate. Multivariate analysis to assess the impact of potential con- founding factors (sex, age, body mass index, endoscopist, tumor location [colon vs. rectum], clinical tumor stage [≥ T2 vs. T1 or scars]) on invisible tattoo will be performed by using a logistic regression model. All tests will be two-sided with a significance level of *P* < 0.05. All statistical analyses will be carried out using SPSS software package (version 22.0; SPSS Inc.).

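### The abstract asks whether safety is similar to intraoperative colonoscopy, but the one safety outcome compared between arms has only difference tests and no bound on excess harm

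*Protocol article*

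**What the plan says.** - **Aim (Abstract, Discussion).** "This trial will investigate whether autologous blood marker achieves similar localization accuracy and safety in laparoscopic colorectal surgery compared to intraoperative colonoscopy". One word, similar, covers both accuracy and safety.
- **Hypothesis.** "Preoperative endoscopic localization with autologous blood is no inferiority to intraoperative colonoscopy localization in small, serosa-negative lesion". It names neither a safety outcome nor a safety margin.
- **Secondary outcomes.** Tattoo-related adverse events, the named secondary endpoint, are confined to one arm: "and intraperitoneal spillage of tattooing agent, will be evaluated in autologous blood group". For the rest, "Surgical complications will be evaluated in both groups", graded by Clavien-Dindo.
- **Sample size and statistical analysis.** The design assumptions concern localization: "success rates of 99 and 95% were assumed for the intraoperative colonoscopy group and the autologous blood group, respectively". With 80% power, a 5% level and a 10-point margin, the article arrives at 110 per group. For comparisons it says: "The differences between the groups were assessed using the t-test, the Mann-Whitney test, Fisher’s exact test, or the χ2 test, as appropriate". On sidedness and level: "All tests will be two-sided with a significance level of" 0.05.
- **Data monitoring, auditing, and interim analysis.** The stopping wording also depends on a statistical difference between treatments, in benefit or in harm.

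**The concern.** To conclude that two treatments are similarly safe, one has to show how large an excess of harm the data rule out. The protocol sets such a limit for localization accuracy and none for safety. Tattoo-related events have no comparator, so surgical complications carry the whole comparative safety question, and the methods stated for comparing groups look for a difference. Failing to find one is weak evidence when the sample was sized for something else.

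At stake is the safety half of the question in the abstract. The article itself gives a route by which tattooing could cause surgical harm: its Discussion notes that spilled blood may distort tissue planes and make dissection harder. It also expects the data to support later multicenter phase III trials. A comparison that merely fell short of significance could be carried forward as reassurance it does not provide.

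**Working it through.** **1. What the 110 per group was built for.** The inputs are 99% and 95% localization success, a 10-point margin and 80% power. With unpooled variance, n = (z_alpha + z_beta)² × (0.99×0.01 + 0.95×0.05) / (0.10 − 0.04)² = (z_alpha + z_beta)² × 0.0574 / 0.0036. This gives 99 per arm at one-sided 0.05 and 126 at one-sided 0.025. The printed 110 does not follow from the stated inputs alone. It equals 99/0.9, which would imply a 10% loss that the article does not state. That is a separate matter, and 110 is taken as given below. What counts here is that no complication rate and no safety margin enter the calculation.

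**2. What 110 per arm can detect for complications.** The article gives no complication rate, so the control rate is an assumption shown as a range. Method: enumerate both binomial distributions (n = 110 each), apply the uncorrected chi-squared test and Fisher's exact test at two-sided 0.05, and sum the probability of non-significance.

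| Control vs blood | Kind of excess | Missed, chi-squared | Missed, Fisher |
|---|---|---|---|
| 5% vs 10% | doubling | 70% | 79% |
| 10% vs 20% | doubling and +10 points | 44% | 52% |
| 15% vs 30% | doubling | 23% | 28% |
| 20% vs 40% | doubling | 9% | 12% |
| 15% vs 25% | +10 points | 54% | 60% |
| 20% vs 30% | +10 points | 60% | 65% |
| 25% vs 35% | +10 points | 63% | 69% |

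Hand check for 10% vs 20% by the normal approximation:
- Null standard error: √(2×0.15×0.85/110) = 0.0481.
- Alternative standard error: √((0.09+0.16)/110) = 0.0477.
- Power: Φ((0.10 − 1.96×0.0481)/0.0477) = Φ(0.12) ≈ 55%, so about 45% are missed, in line with the table.

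By the same approximation, power for a doubling reaches 50% at a control rate of about 9% (slightly above 10% with Fisher) and 80% at about 16%.

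**3. What a non-significant result would leave open.** Two illustrative outcomes, blood versus colonoscopy:
- 28/110 (25.5%) vs 17/110 (15.5%): P = 0.066 (chi-squared) or 0.094 (Fisher). The 95% Newcombe interval for the difference is −0.7 to +20.5 points.
- 12/110 vs 6/110, an observed doubling: P = 0.14 or 0.22, with an upper limit of +13.2 points.

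Both are non-significant, yet both leave open an excess larger than the 10 points tolerated for accuracy.

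**4. What an interval would show if the observed rates were equal.** The half-width is 1.96 × √(2p(1−p)/110): 5.8 points at p = 5%, 7.9 at 10%, 9.4 at 15%, 10.6 at 20% and 11.4 at 25%. A reader can judge that. A bare P value hides it.

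**The case against.** The strongest reply is that the operative sections make no similarity claim for complications. The primary objective is localization accuracy, the secondary objective is tattoo-related adverse events, and the hypothesis concerns localization. The safety wording comes from one loose sentence in the abstract. The list of tests is generic, is to be applied as appropriate, and does not exclude confidence intervals, which a statistical analysis plan may supply. Trials are seldom powered for secondary safety outcomes, and complications are at least graded and assessed in both arms.

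Much of this stands. Lack of power for safety is not an error in itself, and the interval method and the severity cut-off can be left to the analysis plan. It does not remove the mismatch, because the aim and the test family, with sidedness and level, are both stated in the article and do not fit each other.

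Two stronger readings should be resisted:
- A reader might infer that the trial commits itself to declaring similar safety whenever P exceeds 0.05. The text says only that it will investigate whether safety is similar, and it gives no rule for interpreting a non-significant result.
- A reader might infer that a doubled complication rate would usually go undetected. That is so only for control rates below about 9–10%. At 15% or 20% a doubling would usually be found. The outcome is a long, open-ended list of complications, so a low overall rate cannot be presumed.

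**Conclusion.** The point holds as a mismatch between a stated aim and a stated method. The methods given for the only comparative safety outcome cannot establish similar safety, and the design places no bound on excess surgical complications. How much harm could pass unnoticed depends on a rate that the article does not give. For rare outcomes, such as individual or severe complications if they occur in about 5% or fewer (an assumption), most doublings would be missed. For a composite near 20%, few would be, but an excess of 10 points would still be missed more often than not. These figures assume 110 evaluable patients per arm. The primary analysis is not affected. This is a cheap improvement to wording and reporting, not a flaw in the trial's main comparison.

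**What to change.** - **Sample size and statistical analysis:** state that surgical complications (any, and severe by Clavien-Dindo grade) will be reported as a between-arm risk difference, blood minus colonoscopy, with a two-sided 95% confidence interval. State also that P>0.05 will not be read as similar safety. The report should give the largest excess that the upper limit leaves open.
- **Abstract, Discussion:** limit the non-inferiority claim to localization accuracy, and say that the trial will estimate the difference in surgical complications.

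The cost is a few sentences and two intervals from data already being collected, with no added patients or procedures. The price is giving up a similar-safety claim that this design cannot support. If the investigators want to keep that claim, they would need a safety bound justified in advance and a sample size checked against it.

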**Trial registration:**

This study is registered with ClinicalTrials.gov, NCT05597384. Registered 28 October 2022

## Background

Colorectal cancer (CRC) is the third most common cancer and second leading cause of cancer-related deaths in the world [1]. Laparoscopic surgery has become the standard for management of CRC with the advantages of less traumatic procedure, but similar oncological outcomes to open surgery [1–5]. Due to the lack of tactile perception (haptic feedback), surgeons may have misjudgments in patients with small or flat early colon cancer, malignant polyps resected by endoscopic mucosal resection or endoscopic submucosal dissection. Therefore, the accurate localization of a tumor before surgery is important, especially in the early stages of cancer, to clarify the extent of surgical resection.

Several methods are currently being proposed and used to identify the location of tumors. These include endoscopic tattooing with India ink, indocyanine green (ICG), preoperative endoscopic metal clipping with detection using an x-ray or palpation during surgery [6–14]. Intraoperative endoscopy can ensure proper tumor localization but requires longer operation time and additional healthcare resources, such as another physician or an endoscopy unit in the operating room.

Recently, some retrospective studies reported the use of patients’ autologous blood for preoperative colonic localization in CRC with successful detection by laparoscopy [7]. Autologous blood was thought a feasible and safe tattooing agent for preoperative endoscopic localization. Nonetheless, all currently available evidence comes from observational studies that are susceptible to bias. We therefore proposed to conduct this randomized controlled clinical trial (ABILITY) to evaluate the accuracy and safety of autogenous blood marker localization in laparoscopic radical resection for colorectal cancer.

## Methods/design

### Objectives

The primary objective is to compare the localization accuracy of preoperative endoscopic localization with autologous blood versus intraoperative colonoscopy localization for small, serosa-negative lesion which will be resected by laparoscopic colectomy. The secondary objective is adverse events related to endoscopic tattooing.

### Hypothesis

Preoperative endoscopic localization with autologous blood is no inferiority to intraoperative colonoscopy localization in small, serosa-negative lesion which will be performed by laparoscopic colectomy.

### Study design and setting, and participant

The trial is designed as a randomized, controlled, single center no inferiority trial with two parallel groups and a primary endpoint of localization accuracy during laparoscopic colectomy, which will take place in the Department of Gastrointestinal Surgery, Shanghai East Hospital, Tongji University, Shanghai, China (Fig. 1). The participants will be screened for inclusion and exclusion criteria (Table 1) by the reception oncologist. Eligible patients will be invited for study participation at their first visit at Department of Gastrointestinal Surgery. The doctor who sees the patient will give a formal and detailed description of the study and its procedures. Upon the acquisition of patient written informed consent form, patients will undergo assessment.

**Table 1 Tab1:** Key inclusion and exclusion criteria of the trial

Inclusion criteria	Exclusion criteria
• Age from 18 to 80 years • Large lateral spreading tumors that could not be treated endoscopically, malignant polyps treated endoscopically that required additional colorectal resection, and serosa-negative malignant colorectal tumors (≤ cT3) • The tumor located in the colon, middle and high rectum (The lower edge of the tumor located above the peritoneal reflexes) • No distant metastasis • American Society of Anesthesiology score (ASA) class I-III • Performance status of 0 or 1 on Eastern Cooperative Oncology Group scale (ECOG) • Written informed consent	• BMI > 35 kg/m2 • Previous history of gastrointestinal surgery that altered the gastrointestinal anatomy. • Pregnant or lactating women • Severe mental disorder • History of previous abdominal surgery (except cholecystectomy and appendectomy) • Rejection of laparoscopic resection • History of cerebrovascular accident within the past six months • History of unstable angina or myocardial infarction within the past six months • History of previous neoadjuvant chemotherapy or radiotherapy • Comorbidity of emergent conditions like obstruction, bleeding or perforation. • Needing simultaneous surgery for other diseases.

After completing an initial assessment and signing an informed consent form, participants will be randomized with 1:1 ratio into two groups: autologous blood marker group and intraoperative colonoscopy group. The data manager, who will not be involved in eligibility assessment and recruitment of patients, will perform the randomization with a list of randomly ordered treatment identifiers generated by a permuted block design using SAS (version 9.1; SAS Institute Inc.). Although it will not be feasible to blind the surgeons and participants, the researcher performing the statistical analyses will be blinded to the patient group allocation.

This protocol and the informed consent forms have been reviewed and approved by Shanghai East Hospital and Institute Ethics Review Committee. We will obtain a new approval from the Committee if any amendments are made to the protocol or the informed consent form that may have an impact on the conduct of the study or potential benefit of the patient. A signed consent must be obtained from every participant in the ancillary study, if the data collection/request is not covered in the original informed consent process for the main clinical trial. The study has been registered in Clinical-Trial.gov (NCT05597384).

### Intervention

All patients will receive localization and surgery within 1 week after randomization. Endoscopic tattooing with autologous blood and intraoperative colonoscopy will be performed by two experienced endoscopists who has more than thousands of cases colonoscopies and more than 200 cases of endoscopic mucosal resection or endoscopic submucosal dissection.

For patients who will enroll in autologous blood group, the tattooing will be performed at 24–48 hours before the surgery. When the lesion is identified by endoscopy, the patient’s peripheral venous blood will be collected using a 10 ml simple syringe without heparin preparation. Immediately after blood sampling, 2–3 ml of autologous blood will be injected submucosally at the distal side and proximal side of the lesion (about 2 cm below and above the border of the lesion) using a conventional endoscopic needle without submucosal injection of normal saline. The tattooing with autologous blood will consider to be invisible if both distal and proximal spots was not identified. For those receiving autologous blood localization, the case will be applied intraoperative colonoscopy if the autologous blood tattoo will not be identified or inaccurate in the laparoscopic colectomy.

For patients who will enroll in intraoperative colonoscopy group, the patient will be placed in the modified lithotomy position under general anesthesia with endotracheal intubation. The legs will be opened and positioned in padded stirrups to facilitate the insertion and manipulation of the colonoscope during the operation. After routine laparoscopic exploration, CO_2_-insufflated intraoperative colonoscopy will be performed using a flexible videocolonoscope. Upstream small bowel clamping will be applied before intraoperative colonoscopy. During intraoperative colonoscopy, CO_2_ pneumoperitoneum will be maintained by the insufflator so that the laparoscope could guide the colonoscope effectively.

After lesion will be identified, a standard laparoscopic colectomy will be performed by two experienced surgeons who has more than 20 years of experience in colorectal surgery with more than 200 cases per year for all enrolled patients. All abdominal operation of laparoscopy will be videotaped. Anastomosis will be performed using the instrumental method. The specimen will be pulled out through a small median incision under the xiphoid (about 3–8 cm).

For those receiving laparoscopic colectomy, the case will be required to be converted to open surgery if one of the following happens: severe or life-threatening intraoperative complications such as intra-abdominal massive haemorrhage, severe organ damage, or other technical or instrumental factors that require a conversion to open surgery.

### Assessment of outcomes

#### Primary outcome

The primary outcome is the localization accuracy. While checking the intraperitoneal cavity at the start of the surgery, the visibility of tattooing will be first checked. After the complete resection of the colon segment, resected colon specimen will be checked the localization with autologous blood tattooing. An accurate localization is defined as tumors identified both by visible tattoo during surgery and by pathological examination of the resected specimen.

#### Secondary outcomes

The secondary endpoint, which is adverse events related to endoscopic tattooing, such as perforation, abscess formation, peritonitis, post-tattoo fever, post-tattoo abdominal pain, and intraperitoneal spillage of tattooing agent, will be evaluated in autologous blood group. Surgery related complications include peritoneal effusion or abscess formation, hemorrhage (inside abdominal cavity, inside digestive tract), ileus, anastomotic leakage, intestinal fistula, lymphatic leakage, gastroparesis, pancreatitis, lung infection, pleural effusion, urinary tract infection, renal failure, liver failure, cardio-cerebrovascular events (both lower extremities thrombosis, pulmonary embolism, myocardial infarction, arrhythmia, cerebral infarction, etc.), and others. Surgical complications will be evaluated in both groups. Complications will be reported and graded according to the Clavien-Dindo classification of surgical complications.

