### Data collection

Table 2 displays the schematic diagram for the timeline of patient assessment and data collection. Assessment on localization accuracy and safety will be performed by research physicians and recorded by the research nurse within 30-days after the laparoscopic colectomy. All information should be recorded in Case Report Form (CRF) in a timely, truthful and detailed manner. Researchers must input information into the CRF according to protocol requirements, and supervisors appointed by the research center will check the completeness and accuracy of the CRF and guide the research center personnel to make necessary modifications or additions. CRF will hand over data entry to a reliable medical data processor. Text items can only be checked manually after they are entered into the database from CRF. The data manager performs system checks on the information entered the database. Data will be locked upon completion of entry. Any subsequent changes to the database may only be made with the joint written consent of the clinical study leader, the study statistician, and the data manager.

**Table 2 Tab2:** Schematic diagram for the schedule of enrolment, interventions, and assessments

TIMEPOINT	STUDY PERIOD			
	Enrolment	Allocation	Post-allocation	
	−1 to −2 weeks	0	1 week	2 weeks
ENROLMENT:				
Eligibility screen	X			
Informed consent	X			
Allocation		X		
INTERVENTIONS:				
*Autologous blood*			X	
*Intraoperative colonoscopy*			X	
ASSESSMENTS:				
*Physical examination*	X		X	
*Laboratory tests*	X		X	
*Oncology assessment*	X			
*localization accuracy*			X	
*Surgical safety*				X

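### The only named secondary endpoint is assessed in the blood arm alone, so it cannot compare localisation-related harms, and the text and Table 2 give different safety windows

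*Protocol article*

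**What the plan says.** **Endpoint and arm.** The abstract (Methods) states: "The secondary endpoint is adverse events related to endoscopic tattooing". The section Secondary outcomes lists perforation, abscess, peritonitis, fever and abdominal pain after tattooing, and "intraperitoneal spillage of tattooing agent, will be evaluated in autologous blood group". It then gives a second list, of surgery-related complications, and says of these: "Surgical complications will be evaluated in both groups". It adds: "Complications will be reported and graded according to the Clavien-Dindo classification of surgical complications".

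**Comparative statement.** The abstract (Discussion) says the trial will investigate "whether autologous blood marker achieves similar localization accuracy and safety in laparoscopic colorectal surgery compared to intraoperative colonoscopy".

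**Timing.** Under Data collection, accuracy and safety are assessed and "recorded by the research nurse within 30-days after the laparoscopic colectomy". Table 2, in the same section, has a row "Surgical safety" with one mark, in the 2-week post-allocation column, which is its last. The section Intervention states: "All patients will receive localization and surgery within 1 week after randomization".

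**General recording.** The section Adverse events has every adverse event entered on the CRF, whatever its cause, with its relevance to treatment.

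**The concern.** An endpoint defined by tattooing and collected only in tattooed patients describes one arm. It cannot show whether localising with blood is as safe as localising with intraoperative colonoscopy, because nothing matching it is named for the control arm. Perforation and peritonitis are plausible after either endoscopic procedure. If they are reported for one arm only, readers will compare the blood-arm rate with an unstated control rate.

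The timing point concerns what is captured. Leakage, abscess and thromboembolic events are on the protocol's own complication list and can appear after the second week. If staff work to Table 2, the planned contact comes well before the 30 days in the text, and its distance from the operation depends on how soon after randomisation surgery took place.

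**Working it through.** **1. The two event lists side by side (Secondary outcomes).**

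| Event | Tattooing list (blood arm only) | Surgical list (both arms) |
|---|---|---|
| Perforation | named | not named |
| Peritonitis | named | not named |
| Fever | named (after tattooing) | not named |
| Abdominal pain | named (after tattooing) | not named |
| Abscess | named | named |
| Spillage of agent | named | cannot occur without a tattoo |

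Only abscess is named in both lists. The surgical list ends with an open category, so the other events could be reported there, but nothing requires it.

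**2. A group that fits neither list.** Under Intervention, a blood-arm patient whose tattoo is not seen or is inaccurate also has intraoperative colonoscopy. Harm from that procedure is not tattooing-related, so it is outside the named secondary endpoint in either arm.

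**3. Precision of a one-arm count (illustration; zero events is an assumption).** With 0 events in the 110 planned blood-arm patients, the exact one-sided 95% upper limit is 1 − 0.05^(1/110) = 2.7%, and the rule of three gives 3/110 = 2.7%. This limits the blood-arm rate. It says nothing about the difference from control.

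**4. Table 2 converted to days after surgery.** Inputs: assessment at 2 weeks = day 14 after allocation (Table 2); surgery within 1 week of randomisation (Intervention), taken as day 1 to day 7; text window of 30 days after surgery (Data collection).

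- Surgery on day 7: 14 − 7 = 7 days after surgery; 7/30 = 23%.
- Surgery on day 1: 14 − 1 = 13 days after surgery; 13/30 = 43%.
- Day 30 after surgery falls on day 1 + 30 = 31 to day 7 + 30 = 37 after allocation, beyond the last column of Table 2.
- Sensitivity: if the 2 weeks are counted from surgery, or surgery is on the day of randomisation, coverage is 14/30 = 47%.

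On each of these readings, the Table 2 time point covers less than half of the window in the text.

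**The case against.** The strongest reply is that a two-arm safety comparison is planned. Surgical complications are evaluated in both groups and graded by Clavien-Dindo, and all adverse events go on the CRF with their relevance to treatment. This stands. A reader might infer that the trial has no basis for any safety comparison, and the document does not support that. What is missing is a named comparison of localisation-related harms; the data for it should exist.

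It can also be said that the one-arm endpoint matches the formal secondary objective, that the Hypothesis does not mention safety, and that the Background attaches no comparator to safety. The comparative wording comes from the abstract. This is fair, and it is why narrowing that statement is an acceptable alternative remedy.

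Some one-arm reporting is unavoidable. Spillage, and fever or pain in the 24–48 hours between tattooing and surgery, need a tattoo. Intraoperative colonoscopy takes place during the resection itself, so later fever or pain cannot readily be assigned to it. An endpoint of harms attributed to localisation would rest on unblinded judgement in an open-label trial. This stands too, and it argues for counting events regardless of attribution.

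A reader might also infer that the one-arm count would bias the interim stopping rule against blood. The section on interim analysis does not say which outcomes feed that rule, so this cannot be claimed.

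On timing, 2 weeks lies inside 30 days, Table 2 is described as schematic, and the 30-day sentence can be read as an outer limit for recording. A loss of follow-up is therefore not shown. The schedule is also the same for both arms, so it does not by itself bias the comparison. The ascertainment window nevertheless remains unclear.

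**Conclusion.** The point holds in two limited parts.

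First, the named secondary endpoint is non-comparative and cannot support the abstract's between-arm safety statement for localisation-related harms. Four events that can occur in either arm (perforation, peritonitis, fever, abdominal pain) are named for the blood arm only. The planned two-arm comparison of surgical complications is unaffected.

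Second, the safety window is stated inconsistently: 30 days after surgery in the text, against about 7 to 13 days after surgery in Table 2 (23% to 43% of 30 days). This assumes surgery on day 1 to 7 and an assessment on day 14 after allocation. If Table 2 is followed alone, later complications are missed in both arms, and follow-up length varies with the date of surgery.

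Both parts should be corrected. Neither touches the primary endpoint.

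**What to change.** 1. Count perforation, peritonitis, abscess, fever and abdominal pain in both arms, over the same window and regardless of attributed cause, from the adverse event data already on the CRF. Report the risk difference with a confidence interval for each.
2. Keep spillage and pre-operative events after tattooing as descriptive blood-arm data. State where the common window starts. If it starts at the operation, a perforation between tattooing and surgery appears only in the descriptive table and should be shown beside the comparison.
3. If item 1 is not adopted, limit the abstract's comparative safety statement to surgical complications.
4. Reconcile Table 2 with the Data collection text, so that safety is ascertained over one fixed postoperative window in both arms. The text states 30 days.

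The cost is a few more tabulations, a corrected schedule column, and carrying out the 30-day follow-up already stated. Counting regardless of attribution also mixes in background events from surgery, especially fever and pain, so a localisation effect on those is diluted. In return, no unblinded causal judgement is needed. With 110 patients per arm, the comparison of rare events will be imprecise, and the interval should be read as such.
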